### Plans for collection, laboratory evaluation, and storage of biological specimens for genetic or molecular analysis in this trial/future use {33}

There is no anticipated future use of participant blood samples. These samples will be taken only for purposes of RDT diagnosis of malaria infection in the current study. The Study Sponsor, UND, will be responsible for managing requests for access to study data in partnership with CRS according to the data management policies of the funder.

## Statistical methods

### Statistical methods for primary and secondary outcomes {20a}

The intention to treat (ITT) analysis is the primary analysis approach for both the primary objectives. The ITT population includes the first recruited participant from each recruited HH that receives at least one SR product per the cluster randomization schedule and is analyzed according to the randomization schedule.

The primary objective will be examined by comparing the HRs of the first-time malaria infection between each of the two real-life product delivery mechanisms vs. the reference mechanism in the ITT population. The complementary log–log (cloglog) regression model log(-log(1- Θ_kjit_)) = β_0t_ + **x**^t^_kji_**β**_1_ + z_k_ + z_j(k)_ will be applied. Θ_kjit_ is the discrete time HR of participant i from HH j in cluster k at time t, and x_kji_ contains the individual-, HH- and cluster-level factors that include the treatment group (reference, VHT, voucher) and other relevant covariates (e.g., age, gender, HH type, cluster size, etc.). If the data are extremely unbalanced in a categorical covariate (e.g., 99% HHs had the same type of walls) or if a non-ignorable portion of the participants have missing values on a covariate (due to missing at random (MAR) or missing completely at random(MCAR), that covariate may be excluded in the model. z_k_ ~ N(0,σ_1_^2^) and z_j(k)_ ~ N(0,σ_2_^2^) are the random effects at the cluster and HH levels respectively (z_j(k)_ will be only necessary if some HHs contribute more than one individual to the study).

The difference in effectiveness between each of the two real-life delivery mechanisms vs the reference mechanism will be estimated by exp ($$\widehat{\beta }$$), where $$\widehat{\beta }$$ is the estimated regression coefficient associated with the real-life delivery mechanism compared to the reference. The Wald-type 90% confidence interval will be obtained for the HR along with the point estimate exp($$\widehat{\beta }$$). The cloglog model used to analyze the overall infections is similar to the above model with one modification; that is, the cloglog model will include an additional random effect z_i(jk)_ ~ N(0,σ_3_^2^) to capture the correlation among the overall events from the same participant.

The frequency and percentage of AEs and SAEs across clusters among enrolled participants will be summarized by the treatment arm. The AE/SAEs summary will be provided for both clinical diagnoses as well as symptoms. In addition, they will be labeled by Probable, Possible, Plausible (such as dermal events, oral events, Inhalation events), or Unlikely (eye Irritation, headache) due to SR.

Through carrying out a costing study, modeling activities planned in the Project will facilitate projections of SR cost-effectiveness of delivery at scale (using VHTs and vouchers) based on efficacy in specific contexts and delivered as either a stand-alone tool or when combined with other disease control strategies at scale. By identifying effective delivery systems, the operational costs will be reduced making SRs more affordable for MOHs and more feasible for development partners.

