### Sample size {14}

The sample size of the number of clusters and the number of HHs per cluster is based on the assumption of a 40% between-cluster coefficient of variance; a 12-month intervention period; and a 10% loss to follow-up. Since the primary objective is to quantify the difference in effectiveness between each of the two real-life distribution channels and the reference without formal hypothesis testing, we focus on determining a practically feasible sample size that yields a satisfactory precision for the intervention comparisons on the malaria incidence rate. The previous data suggests that the baseline incidence rate in the study area is around 0.5 to 1 per person-year. Figure 1 provides the precision around the intervention comparison at different numbers of clusters and HHs per cluster. When the number of clusters is 16 per arm and the number of HHs per cluster is 40, the upper bound of the CI for the hazard rate (HR) between a real-life delivery system vs. the reference ranges from 1.30 to 1.33 for baseline HR of 0.5 to 1.0 per person year, and the corresponding lower bound ranges from 0.77 to 0.75 if the estimated HR is 1. Further increasing the number of clusters or the number of HHs per cluster does not significantly shorten the CI width and increase the precision of the HR estimation. Given the precision analysis for different sample sizes, we will recruit 16 clusters with 45 HHs per cluster for each of the 3 intervention arms; altogether, 2160 HHs will be recruited.

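### The planned Wald-type 90% interval has no stated small-sample correction for 48 clusters; computed in the usual way it would cover about 86–88%

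*Protocol article*

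**What the plan says.** All references are to the Protocol article.

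- **Model.** Statistical methods {20a} specifies a discrete-time cloglog regression with normal random terms that "are the random effects at the cluster and HH levels respectively". The household term is needed only if a household contributes more than one child. One child per household is enrolled, so in practice the first-infection model has a single random intercept per cluster.
- **Covariates.** The covariate vector "contains the individual-, HH- and cluster-level factors that include the treatment group", together with "other relevant covariates (e.g., age, gender, HH type, cluster size, etc". Cluster size is a cluster-level variable. No list or maximum number is given.
- **Interval.** "The Wald-type 90% confidence interval will be obtained for the HR along with the point estimate". The article does not say whether the standard error comes from maximum likelihood or a restricted method, whether the quantile is normal or t, or what degrees of freedom apply.
- **Size.** Sample size {14}: "we will recruit 16 clusters with 45 HHs per cluster for each of the 3 intervention arms", assuming "a 40% between-cluster coefficient of variance; a 12-month intervention period; and a 10% loss to follow-up". The same section says the aim is precision and that no hypothesis will be formally tested. Trial design {8} labels the trial exploratory.

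**The concern.** The treatment contrast rests on differences between 48 clusters. With a between-cluster coefficient of variation of 0.40, most of its variance lies between clusters. Two features of an ordinary Wald interval then make it too short:

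- Maximum likelihood estimates the between-cluster variance without allowing for the fixed effects already fitted, so the standard error is too small.
- A normal quantile ignores the fact that this variance is itself estimated from limited degrees of freedom.

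Each cluster-level covariate uses a further between-cluster degree of freedom and adds to both effects.

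Because nothing is tested, the hazard ratio and its interval carry the primary result. The introduction says the evidence should inform whether delivery channels are equivalent in impact and that findings will go to WHO. Readers will look at the upper bound to judge how much effectiveness a channel could lose. With symmetric errors, coverage of 88% means about 6% error per side, and 86% about 7%, where 5% is intended.

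**Working it through.** **Inputs.** From Sample size {14}: 16 clusters in each of 3 arms (48 in all), 40 households per cluster in the precision statement, 45 recruited, coefficient of variation 0.40, 12 months, 10% loss, baseline rate 0.5 to 1.0 per person-year. From {20a}: a 90% Wald-type interval. Assumed: q cluster-level covariates with no true effect, q = 0 to 5.

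**Step 1: reproduce the article's precision.**

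SE(log HR) = √{(2/16)[CV² + 1/(m × 0.9 × p)]}, with m = 40 and p = 1 − exp(−rate).

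- Rate 0.5: p = 0.393, events per cluster 36 × 0.393 = 14.2, SE = √{0.125 × (0.16 + 0.0706)} = 0.170. The 90% interval with 1.645 is 0.756 to 1.322.
- Rate 1.0: p = 0.632, events per cluster 22.8, SE = √{0.125 × (0.16 + 0.0439)} = 0.160. The 90% interval is 0.769 to 1.300.

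The article gives upper bounds of 1.30 to 1.33 and lower bounds of 0.77 to 0.75, so a 90% interval reproduces its figures. (The wider interval belongs to the lower rate; the article lists them in the opposite order.) A 95% interval does not fit, with upper bounds of about 1.37 to 1.40.

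**Step 2: coverage in closed form.** For balanced cluster summaries, the maximum-likelihood variance is RSS/48 and the unbiased one is RSS/df, with df = 48 − 3 − q. Hence:

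- ML standard error with z: coverage = P(|t_df| < 1.645 × √(df/48)).
- ML standard error with t: the same, with the t quantile in place of 1.645.
- Width needed for 90%, relative to ML with z: √(48/df) × t(0.95, df)/1.645.

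For q = 0: 1.645 × √(45/48) = 1.593, and P(|t_45| < 1.593) = 88.2%. The width ratio is 1.033 × 1.679/1.645 = 1.055.

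**Step 3: simulation of the model.** Random-intercept cloglog model with 48 clusters, 45 children each, 13 intervals, 10% loss, CV 0.40 and true HR 1. It was fitted by maximum likelihood with 21-point quadrature and a constant baseline hazard, 6,000 runs per setting (Monte Carlo SE about 0.3 points).

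| q | ML + z, closed form | ML + z, simulated (rate 0.5 / 1.0) | ML + t, closed form | ML + t, simulated | Width ratio for 90% |
|---|---|---|---|---|---|
| 0 | 88.2% | 88.4 / 88.0% | 88.9% | 88.7–89.0% | 1.055 |
| 1 | 87.8% | 88.0 / 87.6% | 88.5% | 88.4–88.8% | 1.067 |
| 3 | 86.9% | 86.7 / 87.3% | 87.7% | 87.6–88.2% | 1.093 |
| 5 | 85.9% | 85.3 / 85.8% | 86.8% | 86.1–86.7% | 1.121 |

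At rate 0.5 the mean Wald SE was 0.157, against an empirical SD of 0.162 (q = 0) and 0.174 (q = 5). The standard error itself is short, which is why the t quantile alone recovers less than one point. A corrected variance with z gives 89.2–89.3% in closed form. Both corrections together give 90% by construction. A separate cluster-level normal-approximation simulation (4,000 runs per setting) of a restricted-type variance with t gave 89.9–91.0%.

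**Step 4: effect on a bound.** For an upper bound of 1.32, exp(ratio × ln 1.32) is 1.340 (q = 0), 1.345 (q = 1) and 1.354 (q = 3).

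**The case against.** The strongest reply is that the article commits to neither maximum likelihood nor a normal quantile. A Wald-type interval is an estimate plus or minus a quantile times a standard error, so a restricted-type standard error with a t quantile also qualifies. The proposed remedy could be adopted without changing the quoted sentence. Estimator and degrees-of-freedom rules are normally settled in the statistical analysis plan, which is promised but not shown. This stands. A reader might infer that the article prescribes a z interval from maximum likelihood and that its 90% interval is therefore shown to be wrong; the text does not support that.

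The lower end of the range is also an assumption. Cluster size is the only cluster-level covariate named for the intention-to-treat model, as an example. Others are possible: Sequence generation {16a} allows stratification on malaria prevalence or demographics, the clusters mix refugee and host villages, and the per-protocol analysis in {20b} may add cluster product coverage. None of this fixes a number, so coverage near 86% should not be read as the expected result. The simulated covariates were null. Informative ones would reduce between-cluster variance and shorten the interval, so the width ratios compare methods within one model and do not forecast the reported width.

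A reader might also infer that the sample size fails or that a false claim of equivalence would follow. Neither is supported. At the design SE, replacing z by t on 45 degrees of freedom moves the upper bounds only from 1.300–1.322 to 1.308–1.330, still within the stated 1.30–1.33. No margin or decision rule is attached to the interval.

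What remains is that the article does fix the model type, the interval type and the use of cluster-level factors for a 48-cluster contrast. The ordinary execution of those choices under-covers, even with a t quantile.

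**Conclusion.** The point holds conditionally and is minor. The shortfall is about 2 points with no or one cluster-level covariate, about 3 with three and about 4 with five, if the usual maximum-likelihood standard error and 1.645 are used. With a t quantile and the same standard error, coverage is about 87–89%; the simulated values at q = 5 are slightly lower, 86.1–86.7%.

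These figures rest on CV 0.40, equal cluster sizes, normal random effects, null covariates and, in the simulation, a constant baseline hazard and a cluster intercept only. The overall-infections model, which adds a participant effect, was not simulated. The result is a calibration improvement to the trial's main inferential output. It is not evidence of an error in the article.

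**What to change.** Before analysis, add a short statement to the analysis plan that:

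- names the estimator and computes the 90% interval from a degrees-of-freedom-corrected between-cluster variance (for example restricted pseudo-likelihood), with a t quantile on 48 − 3 − q degrees of freedom, or uses a parametric bootstrap;
- lists the cluster-level covariates in advance and keeps q small.

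Both parts of the correction are needed, since either alone leaves coverage below 90%.

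The cost is a slightly wider interval: about 5–7% on the log scale with zero or one cluster-level covariate (an upper bound of 1.32 becomes about 1.34–1.35) and about 9% with three. Recruitment, data collection and follow-up do not change. Point estimates may shift slightly if the estimator changes. The Trial status section places enrolment in July to August 2024, after protocol version 12, so on the article's own timeline the rule can still be set in advance.

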### Adverse event reporting and harms {22}

An AE includes any noxious, pathological, or unintended change in anatomical, physiological, or metabolic functions as indicated by physical signs, symptoms, and/or laboratory-detected changes occurring in any phase of the clinical study associated with the study intervention. This definition includes an exacerbation of pre-existing conditions or events, intercurrent illnesses. A SAE is any untoward medical occurrence that results in death, is life-threatening, results in persistent or significant disability/incapacity, requires in-patient hospitalization or prolongation of existing hospitalization, or is a congenital anomaly/birth defect in the offspring of a study participant. In addition, important medical events that may jeopardize the participant or may require intervention to prevent one of the other outcomes listed above will be considered serious.

All SAEs will be recorded on the appropriate SAE case report form, followed through resolution by a study physician, and reviewed by a study physician.

Symptomatic uncomplicated or severe malaria infection will be coded as AEs as will any other acute illness, throughout the 12 months of the study follow-up phase. Clinical malaria will be recorded in the same fashion as other AEs. In general, uncomplicated malaria will constitute an AE and severe malaria will constitute an SAE. Anticipated day-to-day fluctuations of pre-existing conditions that do not represent a clinically significant exacerbation need not be considered AEs. Discrete episodes of chronic conditions occurring during a study period will be reported as AEs to assess changes in frequency or severity. Pre-existing conditions or signs and/or symptoms (including any that are not recognized at study entry but are recognized during the study period) present in a participant prior to the start of the study will be recorded on the participant’s Case Report Form.

AEs will be documented in terms of a medical diagnosis. When it is not possible to make a specific medical diagnosis, the AE will be documented in terms of signs and/or symptoms observed by the investigator or reported by the participant at each study visit. Any hospitalization will be considered a SAE.

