AEs to be recorded as endpoints will be pre-defined based on SCJ toxicology reports of “probable,” “possible,” “plausible,” and “unlikely”:Probable: sensory irritation (oral and dermal)Possible: nausea/vomiting (oral), skin irritation/rash (dermal), runny nose (inhalation)Plausible: salivationUnlikely: eye irritation, headache

AEs and SAEs will be recorded throughout the study. SAEs and the study reports will also be provided to the Makerere University School of Public Health Research and Ethics Committee as required by their current Standard Operating Procedures. AEs will be recorded at time of product replacement and/or when a participant reports for malaria testing. In addition, participants will be informed they can contact study staff anytime they experience an AE. SAEs will be recorded at time of death, hospitalization. Assessment of SAE relatedness to intervention will be conducted by the health facility physician and the study coordinator, in coordination with the local PI in-country with confirmation/verification by the DSMB Medical Monitor based on the study clinician SAE report and trends in other SAE datasets.

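### Adverse events are labelled as more or less likely due to the repellent from a symptom list set in advance; this is expectedness, not causality, and it overlaps with the clinical SAE assessment

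*Protocol article*

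**What the plan says.** Assessing the safety of the product is a secondary objective (Protocol article, Objectives {7}). Outcomes {12} counts solicited and unsolicited AEs and SAEs over the 12-month intervention period.

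The statistical methods section {20a} first tabulates frequency and percentage of AEs and SAEs by arm, for diagnoses and for symptoms. It then adds a label: "they will be labeled by Probable, Possible, Plausible (such as dermal events, oral events, Inhalation events), or Unlikely (eye Irritation, headache) due to SR".

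The harms section {22} gives the origin of the classes: "AEs to be recorded as endpoints will be pre-defined based on SCJ toxicology reports". Four classes follow, each defined by symptoms.

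For serious events the same section describes something different: "Assessment of SAE relatedness to intervention will be conducted by the health facility physician and the study coordinator", together with the local investigator and "with confirmation/verification by the DSMB Medical Monitor based on the study clinician SAE report and trends in other SAE datasets". For safety reporting it describes no matching step for non-serious events.

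**The concern.** A toxicology profile supports a statement about which symptoms are expected from a product. It does not support a statement that a particular event in the trial was, or was not, due to that product. Section {20a} moves from the first to the second by attaching the pre-set class to each observed event and wording it as a likelihood of being caused by the repellent.

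The consequence is a safety table that looks like a causality finding but contains no causal information from the trial. It could tell policy makers that the headaches and eye irritations seen in these children were unlikely to be caused by the product, when nothing observed in the trial could have produced a different answer. In the other direction, ordinary childhood rashes and runny noses would be listed as possibly caused by it.

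**Working it through.** No arithmetic applies: the article gives no AE rate and no figure on this point. The check sets the sections side by side.

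**1. What decides the label.** Section {22} assigns symptoms as follows.

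| Class | Symptoms in {22} |
|---|---|
| Probable | sensory irritation, oral and dermal |
| Possible | nausea or vomiting (oral), skin irritation or rash (dermal), runny nose (inhalation) |
| Plausible | salivation |
| Unlikely | eye irritation, headache |

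The only input is the symptom. Timing, recurrence on re-exposure, alternative diagnosis and frequency do not enter. Hence:

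- eye irritation or headache caused by the product: *Unlikely*, in every case;
- rash or runny nose not caused by the product: *Possible*, in every case;
- any symptom outside the list: no class stated.

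**2. Whether the by-arm tables supply the missing causal information.** The three arms are study personnel, VHT and voucher delivery of the same product (Explanation for the choice of comparators {6b}), and Who will be blinded {17a} confirms that there is no placebo. A by-arm difference in AE frequency therefore compares delivery channels. A reaction that the product causes equally in all arms produces no difference. The same limit applies to the DSMB's comparison of AE and SAE rates across the three arms in {21a}.

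**3. Whether another relatedness judgement is described for safety reporting.** For SAEs, yes: {22} has clinicians assess each case and the Medical Monitor verify it. For non-serious AEs, none is described. So for these events the symptom label is the only statement about the product that reaches the safety summary.

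**4. Whether the two systems are kept apart.** They are not. In {20a} the sentence before the labels speaks of the AE/SAE summary, and the labels then apply to both kinds of event. An SAE presenting as a listed symptom would carry one verdict from the list and another from the clinicians. The DSMB section {21a} triggers notification for SAEs judged at least possibly related, which is close to the list's own vocabulary, so the text should say which verdict counts.

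**5. Whether the two sections give the same mapping.** That depends on how the bracket in {20a} is read.

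- If it belongs to *Plausible* alone, dermal, oral and inhalation events are *Plausible*. This contradicts {22}, where *Plausible* holds only salivation.
- If it covers *Probable*, *Possible* and *Plausible* together, the sections agree.

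The text does not settle it, so this is an ambiguity and not a proven contradiction.

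**The case against.** The strongest reply is that no event is hidden. The main safety result is a full count by arm, diagnosis and symptom, including unsolicited events, and the label is an addition to it. That is correct, and it limits the point to the label.

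A reader might infer more than the article supports:

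- **That a reaction of an unexpected type would be reported as *Unlikely*.** The article does not say so. That class names two symptoms, both on the list. An unlisted reaction has no class, which is a gap in the scheme and not a rule.
- **That the safety result merely repeats the manufacturer's list.** Only the relatedness label does; the counts come from the trial.
- **That vomiting in a child with malaria would routinely be put down to the product.** Section {22} records AEs as a medical diagnosis and falls back on signs and symptoms only when no specific diagnosis can be made, and it codes symptomatic malaria as an AE. Such a child would primarily appear under malaria.
- **That nobody ever judges a non-serious event.** The follow-up section under {18a} has the physician and study coordinator decide whether an illness or injury is due to the study product, and {11b} refers to clinical assessment of AEs. The first serves payment of fees and the second ends participation. Neither is said to feed the safety summary.

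It can also be said that case-by-case grading of non-serious AEs belongs in the full protocol or SAP, which are not shown. Its absence is accordingly not the criticism. The criticism is of a rule that the article does state. If a causality grading exists elsewhere, it would still have to be reconciled with {20a}.

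**Conclusion.** The point holds as a defect of labelling and interpretation. As written, the plan reports a causal likelihood that is a fixed function of symptom type. For eye irritation and headache the label is *Unlikely* in all cases; for rash and runny nose it is *Possible* in all cases. Because every arm receives the repellent, nothing else described in the summary corrects this for non-serious events. SAEs may carry two relatedness labels with no statement of which prevails.

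The number of events affected cannot be derived from the article. Event counts and the malaria outcome are untouched. The conclusion assumes that the classes named in {20a} are those of {22}; the shared class names and the shared content of *Unlikely* make that the natural reading. The correction is worth making because a secondary objective rests on this table and the change is almost free.

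**What to change.** In {20a} and {22}:

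1. Present the four toxicology classes as an expectedness flag and delete the phrase that attributes events to the repellent.
2. Use one symptom-to-class mapping in both sections, and add an *unlisted* class for any symptom not named.
3. State that the clinical assessment, with verification by the DSMB Medical Monitor, alone gives the relatedness of SAEs.
4. State that no conclusion on product causality for non-serious AEs is drawn from the flag.

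Timing of symptoms relative to product replacement may be tabulated descriptively, but only if onset and replacement dates are captured. The article mentions recording a product code at installation and replacement ({11a}), not a date. It collects AEs at replacement or when a child reports for malaria testing, without mentioning onset. Voucher households also hang the product themselves.

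A before-and-after comparison has no sound basis in what is described. Earlier conditions "present in a participant prior to the start of the study will be recorded on the participant’s Case Report Form", but that is not a rate on the same footing as 12 months of follow-up, and most children receive presumptive malaria treatment just before the first product.

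The cost is a few sentences in two sections, with no new visits, samples or participants. The report loses a simple count of events unlikely to be related to the product.
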